| **IEC** | Independent Ethics Committee |
| **IRB** | Institutional Review Board |
| **PI** | Principal Investigator |
| **SAE**  **UCSF** | serious adverse experience  University of California, San Francisco |

Protocol Synopsis

| **TITLE** | **Optimal Location of Local Anesthetic Injection for Ultrasound-guided Interscalene Nerve Block** |
| --- | --- |
|  |  |
| **SPONSOR** | [name] |
|  |  |
| **FUNDING ORGANIZATION** | Unfunded (miscellaneous departmental funding) |
| **NUMBER OF SITES** | 1 |
|  |  |
| **RATIONALE** | Patients undergoing shoulder surgery typically receive an ultrasound-guided interscalene nerve block preoperatively for postoperative pain control. Currently, the local anesthetic is injected either periplexus (in the space surrounding the interscalene brachial plexus in between the anterior and middle scalene muscles) or intraplexus (in between the nerve roots) depending on the preference of the anesthesiologist performing the block. However, the optimal location for injection of local anesthetic during ultrasound-guided interscalene nerve block is unknown.  We will prospectively randomize patients undergoing shoulder arthoscopy at the UCSF Orthopaedic Institute to receive either local anesthetic injection periplexus (circumferentially around the  interscalene plexus) or a single injection in between the nerve roots. |
|  |  |
| **STUDY DESIGN** | *This is a randomized, blinded study.* |
|  |  |
| **PRIMARY OBJECTIVE** | We hypothesize that local anesthetic injection intraplexus (meaning in between the nerve roots) rather than periplexus (circumferentially around plexus in between the scalene muscles) leads to faster onset of the interscalene block. The primary outcome variable will be time to onset of motor block. |
|  |  |
| **SECONDARY OBJECTIVES** | We hypothesize that the intraplexus approach will have a longer block duration, thus leading to reduced opioid consumption and greater  patient satisfaction postoperatively. We also hypothesize that the intraplexus technique will need to a faster procedure time, thus improving efficiency.  Secondary outcome variables that we will also investigate include: time to onset of sensory block, duration of nerve blockade, highest NRS pain score in the post anesthesia recovery unit and  postoperative day 1, block performance time, patient satisfaction score, perioperative opioid use, perioperative analgesic consumption, incidence of paresthesias, number of needle passes, incidence of postoperative nausea, vomiting, constipation, and any other complications. |
|  |  |
| **NUMBER OF SUBJECTS** | 208 |
|  |  |
| **SUBJECT SELECTION**  **CRITERIA** | Inclusion Criteria:  Age at least 18 years old, ASA I-II classification, scheduled for shoulder surgery  Exclusion Criteria:  Age younger than 18, non-English speaking, any contraindication for regional anesthesia, such as allergy to local anesthetics or opioids, coagulopathy or severe thrombocytopenia, infection at  puncture sites, pre-existing neuropathy in operative limb, need for postoperative nerve function monitoring, pulmonary disease or low baseline oxygen saturation, dementia, patient refusal, and high preoperative opioid requirements. |
|  |  |
| **TEST PRODUCT, DOSE, AND ROUTE OF ADMINISTRATION** | *25mL Ropivacaine 0.5% will be administered once via intraplexus brachial plexus block.* |
|  |  |
| **CONTROL PRODUCT, DOSE AND ROUTE OF ADMINISTRATION** | *25mL Ropivacaine 0.5% will be administered via extraplexus brachial plexus block.* |
|  |  |
| dURATION OF SUBJECT PARTICIPATION AND DURATION OF STUDY | Subjects will be on study for up to 15 days  **Screening:** up to 7 days  **Treatment:** 1 day  **Follow-up:** 7 days  The total duration of the study is expected to be 2 years. 24 months for subject recruitment and 24 months for final subject follow-up. |
| **E** |  |
| **CONCOMMITANT MEDICATIONS** | Allowed: midazolam, fentanyl, lidocaine, propofol, sevoflurane, desflurane, dexamethasone, ondansetron, prochlorperazine, metoclopramide, meperidine  Prohibited: Hydromorphone, ketorolac |
|  |  |
| **Efficacy Evaluations** |  |
| ***Primary endpoint*** | - Time to onset of motor block (loss of shoulder abduction) |
| ***Secondary endpoints*** | - Time to onset of sensory block - Duration of nerve blockade - Highest pain score in the post-anesthesia recovery - Highest pain score on post operative day 1 - Block performance time - Patient satisfaction score - Perioperative opioid use - Perioperative analgesic consumption - Number of needle passes - Block failure - Recovery room length of stay - Incidence of postoperative nausea, vomiting, constipation, and any other complications (hoarseness, shortness of breath, Horner’s syndrome, nerve injury, local anesthetic toxicity, infection at insertion site) - Incidence of paresthesias |
| **Safety Evaluations** | Incidence of adverse events will be recorded and monitored during the study. |
| **Planned Interim Analyses** | Serious adverse events will be monitored by an independent data monitoring committee on an ongoing basis throughout the study. |
|  |  |
| **STATISTICS**  **Primary Analysis Plan** | This study is designed as a prospective two treatment parallel-design study. The primary outcome is the time to block onset. Time-to-event data will be compared using the log-rank test. Assuming a true hazard  ratio of 0.65, power of 0.8 and alpha of 0.05, a sample size of 104 patients per group is needed. This is based on the assumption that the total number of events will be 172. |
| **Rationale for Number of Subjects** | The estimated sample size for a two-sample comparison of survivor functions for the primary outcome variable of time to onset of motor block using the Freedman method for log-rank test with a hazard ratio of 0.65, Power of 0.8 and alpha of 0.05, was a total of 208 patients for the two groups, assuming a total number of 172 events. |

# BACKGROUND

Interscalene nerve blocks are used routinely for postoperative pain control of patients undergoing shoulder surgery. There is considerable evidence that ultrasound guidance increases the efficacy and decreases the performance time of interscalene blocks compared to landmark or nerve stimulation techniques (1,2). However, the optimal location for local anesthetic injection during ultrasound-guided interscalene nerve blocks is not known.

## Overview of Clinical Studies

Recent clinical studies suggest that subfascial injection results in faster block onset and success compared to conventional extrafascial techniques (3). Missair et al. compared extrafascial versus subfascial injection of local anesthetic for popliteal sciatic nerve block in a recent prospective randomized study of sixty patients (4). They found that the placement of the needle tip beneath the fascial sheath of the sciatic nerve resulted in greater sensory blockade (63% in the extrafascial group vs. 90% in the subfascial

group). This study suggests that subfascial injection of local anesthetic significantly improves the efficacy of the nerve block. One study conducted by Spence et al. examined subfascial versus extrafascial injection of local anesthetic in ultrasound-guided interscalene nerve blocks (5). This prospective randomized study of 170 patients

found no difference between the two groups in block onset or block quality. However, the duration of block was significantly longer in the subfascial group. Unfortunately, this study had several problems. They changed their protocol after enrolling 15 patients such that subsequent patients received a different dose of the local anesthetic. Additionally, although they powered the study for 208 patients, they only based the primary outcome of onset of motor block on 155 patients. Multiple injections were allowed in the subfascial group. We hypothesize that a single injection of local anesthetic between the

nerve roots (subfascial) compared to the traditional approach of circumferential, multiple injections around the interscalene plexus (extrafascial) will result in faster onset of nerve blockade, longer duration of blockade and greater patient satisfaction.

# STUDY RATIONALE

Although both intraplexus and extraplexus approaches to the interscalene brachial plexus blocks are performed, one approach may have benefits over the other. Previous studies in popliteal nerve blocks have found that the intraplexus approach was superior in terms of faster onset.

## Risk / Benefit Assessment

There are very rare, but serious risks to peripheral nerve blockade, including infection at the puncture site, bleeding at the puncture site, local anesthetic toxicity, anaphylaxis, and nerve injury. With interscalene nerve blockade, there is also a risk of Horner's syndrome, hoarseness, and respiratory distress. The more common risk of peripheral nerve blockade, occurring in less than 10% of blocks at the Orthopaedic Institute, is failure of the nerve block to provide adequate analgesia in the corresponding anatomical site. This can be easily treated postoperatively by either administration of IV pain medications or a postoperative nerve block. Patients undergoing nerve blocks are advised to protect the operative limb in a sling until numbness from the block has resolved. The numbness resulting from the nerve block is a common and desired side effect. Of note, these risks are not related to patient participation in the study, but rather are the risks of peripheral nerve blockade which patients would receive even if they were not part of the study.

Specific study risks include a potential loss of privacy for patients that are involved in the study. There is a potentially higher risk of transient paresthesia in the group receiving intraplexus interscalene nerve blocks, which we will be recording. There is also a risk with randomization that the patients will be assigned to a treatment program by chance and the treatment they receive may prove to be less effective or to have more side effects than the other study treatment or other available treatments.

**Steps taken to minimize risk to subjects**:

Nerve blocks are performed under sterile conditions with topical application of chlorhexidine to minimize risk of infection. Ultrasound guidance is used to ensure avoidance of needle-to-nerve contact and intravascular injection of local anesthetic. Intravascular injection is prevented by frequent aspiration during local anesthetic injection. In addition to the use of ultrasound real-time guidance, intraneural injection is prevented by performing the block on awake patients with minimal sedation such that they are able to report any pain or paresthesia on injection. Intraneural injection is

also identified by increased resistance on injection. Visualization of local anesthetic spread around the desired nerve is highly predictive for a successful block.

In this study, the preoperative and postoperative nerve blocks are performed in the preoperative holding area and post anesthesia recovery area, respectively. In both locations, the blocks are performed under continuous non-invasive blood pressure and pulse oximetry monitoring. Administration of sedation is minimized so that patients can report paresthesias, should they occur. Emergency medications and equipment is readily available.

The subjects in this study will have a more thorough post-anesthesia follow-up for pain and other side effects. Understanding the optimal location for local anesthetic deposition for peripheral nerve blocks which result in greater patient comfort following ambulatory shoulder arthroscopy is of benefit to society. Complications from single-shot peripheral nerve blockade overall and at our institution, have been extraordinarily rare. Interscalene nerve blocks are commonly employed in anesthetic practice.

# STUDY OBJECTIVES

## Primary Objective

The primary objective is to assess the time to motor onset of interscalene brachial plexus block, as measured by the loss of shoulder abduction, for two approaches to interscalene block (intraplexus and extraplexus)

## Secondary Objectives

- Time to onset of sensory block
- Duration of nerve blockade
- Highest pain score in the post-anesthesia recovery
- Highest pain score on postoperative day 1 and at postoperative week 1
- Block performance time
- Patient satisfaction score
- Perioperative opioid use
- Perioperative analgesic consumption
- Number of needle passes
- Block failure
- Recovery room length of stay
- Incidence of postoperative nausea, vomiting, constipation, and any other complications (hoarseness, shortness of breath, Horner’s syndrome, nerve injury, local anesthetic toxicity, infection at insertion site)
- Incidence of paresthesias

# STUDY DESIGN

## Study Overview

This is a single center, blinded, randomized trial. 208 of subjects are planned. Each subject will be administered a single injection of ropivacaine 0.5% either intraplexus or extraplexus prior to their shoulder surgery. Subjects will be assigned to the treatment group in random order. Evaluations will be taken in one-minute intervals after placement of the block until loss of motor or sensation is observed. Subjects will undergo a standardized general anesthetic. Sensory exam will be reevaluated in the recovery room. Patients will be contacted via telephone on post-operative day 1. Data from their 1 week postoperative visit will be recorded.

Screening data will be reviewed to determine subject eligibility. Subjects who meet all inclusion criteria and none of the exclusion criteria will be entered into the study.

The following treatment regimens will be used:

Experimental treatment –interscalene injection performed intraplexus (between C5-C6 nerve roots)

Comparator – interscalene injection performed extraplexus (anterior and posterior to brachial plexus in interscalene groove)

Total duration of subject participation will be two weeks. Total duration of the study is expected to be 24 months.

# Criteria for evaluation

## Primary Efficacy Endpoint

Time to loss of shoulder abduction. Patient will be sitting upright and instructed to abduct arm every 1 minute until they are no longer able to.

## Secondary Efficacy Endpoints

- Time to onset of sensory block – evaluated by detection of decreased sharpness of contralateral side. This will be evaluated for supraclavicular, axillary, musculocutaneous, median and ulnar nerve distributions.
- Duration of nerve blockade (time from block completion to time patient reports the block started to wear off and no longer providing pain relief)
- Highest pain score in the post-anesthesia recovery unit (using numerical rating scale from 0-10 pain, 0 is no pain, 10 is worst imaginable pain)
- Highest pain score on postoperative day 1 (using numerical rating scale from 0-10 pain, 0 is no pain, 10 is worst imaginable pain), at rest and with movement
- Block performance time - time from block needle insertion to the time that all of the local anesthetic was injected
- Patient satisfaction score – scale from 0-10. Zero is unsatisfied. 5 is neutral and 10 is extremely satisfied.
- Perioperative opioid use – total opioids used preoperative, intraoperative, and postoperatively will be recorded
- Perioperative analgesic consumption – acetaminophen, ibuprofen, ketorolac usage perioperatively
- Number of needle passes - number of times the needle was re-advanced after being withdrawn during block placement
- Block failure - lack of sensory exam consistent with interscalene block in the recovery room or need for repeat interscalene block in recovery room
- Recovery room length of stay (time from entering recovery room to time that discharge criteria met)
- Highest pain score at one week postoperative week visit (0-10 with zero being no pain and 10 worst imaginable pain)

## Safety Evaluations

Incidence of:

- - Postoperative nausea and vomiting
  - Constipation
  - Hoarseness
  - shortness of breath
  - Horner’s syndrome
  - local anesthetic toxicity – any metallic taste in the mouth, tinnitus, altered mental status, hemodynamic instability related to block placement
  - infection at insertion site
  - paresthesias
  - nerve injury (defined as persistent nerve deficit)

# SUBJECT SELECTION

## Study Population

Subjects who are scheduled for an ambulatory arthroscopic shoulder surgery who meet the inclusion and exclusion criteria will be eligible for participation in this study.

## Inclusion Criteria

1. Male or female ≥18years of age at time of surgery.
2. ASA I-II classification, scheduled for ambulatory shoulder surgery at the UCSF Orthopaedic Institute.
3. Written informed consent (and assent when applicable) obtained from subject or subject’s legal representative and ability for subject to comply with the requirements of the study.

## Exclusion Criteria

1. Pregnant during participation in the study.
2. Non-English speaking
3. Any contraindication for regional anesthesia, such as an allergy to local anesthetics or opioids, coagulopathy or severe thrombocytopenia, infection at puncture sites, pre-existing neuropathy in operative limb, need for postoperative nerve function monitoring
4. History of pulmonary disease or low baseline oxygen saturation
5. History of dementia
6. High preoperative opioid requirements

# Concurrent Medications

All subjects should be maintained on the same medications throughout the entire study period, as medically feasible, with no introduction of new chronic therapies.

## Allowed Medications and Treatments

Standard therapy for anesthesia for shoulder surgery is allowed except for treatments noted in the exclusion criteria described above and as noted in the prohibited medications section below. 

Prohibited Medications and Treatments

The following medications are prohibited during the study and administration will be considered a protocol violation.

- Intraoperative ketorolac or hydromorphone

# STUDY TREATMENTS

## Method of Assigning Subjects to Treatment Groups

Up to 208 eligible patients will be randomly assigned to intraplexus or extraplexus treatment groups in a 1:1 ratio using an Excel computer-generated randomization scheme developed by the study data management provider. The allocated group will be written on a paper in a sealed, opaque envelope that will be provided only to the anesthesia provider performing the block.

## Blinding

Due to the objectives of the study, the identity of test and control treatments will not be known to investigators, research staff, or patients. The following study procedures will be in place to ensure double-blind administration of study treatments.

Access to the randomization code will be strictly controlled. The study blind will be broken on completion of the clinical study and after the study database has been locked. Investigators will not be made aware of their subjects’ treatment assignments. All providers, who administer pain medications to the patient, will be blinded to their treatment assignment.

During the study, the blind may be broken **only** in emergencies when knowledge of the patient’s treatment group is necessary for further patient management. When possible, the Investigator should discuss the emergency with the Principal Investigator prior to unblinding.

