### Administration Instructions

**For the placement of the interscalene block, the patient may receive any of the following medications:**

- Midazolam: 0-4mg IV
- Fentanyl: 0-100mcg IV
- Ropivacaine 0.5%: 25mL for interscalene block

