### Other Clinical Procedures

**Interscalene nerve block:**

Patients at the Orthopaedic Institute undergoing shoulder arthoscopy typically receive a preoperative ultrasound-guided interscalene nerve block. Patients in the control group will have local anesthetic injected circumferentially around the interscalene brachial plexus. Patients in the experimental group will have a single injection of local anesthetic placed inbetween the C5- C6 nerve roots. Light sedation is usually administered via the patient's IV during performance of the block. These blocks are performed in the preoperative holding area, with the patients receiving continuous non-invasive blood pressure and pulse oximetry monitoring until being transported into the operating room.

An study investigator (not involved in block placement) will assess motor and sensory block until the onset of block or until the patient is taken to the operating room. From this point forward, patients in both groups are treated identically. All patients will subsequently undergo a general anesthestic.

Postoperatively, if the patient has poor pain control with intravenous opioids, they will be evaluated by an anesthesiologist. A nerve block may be repeated postoperatively if deemed necessary. This nerve block occurs in the post anesthesia recovery unit under continuous noninvasive blood pressure and pulse oximetry monitoring. Patients requiring postoperative nerve blocks will continue to participate in the study, and the number of patients requiring such blocks will be tabulated and analyzed as one of our outcome variables. All patients will be asked to rate their pain and will be provided a pain diary while in the recovery unit.

On postoperative day 1, an anesthesiologist will call the patient and review the questions on the pain diary and solicit responses from the patient. The patient will not be asked to return the pain diary -- it is meant to serve as a guide for the patient as to what questions they will be asked during these brief, approximately 5 minute, phone calls. If the patient's block has not yet resolved by the time of the follow-up phone call on postoperative day 1, then the patient will be called daily until resolution of their block, typically by postoperative day 2.

The patients will be seen by the orthopedic surgery team on 1 week postoperatively and will be assessed for any adverse events as well as their highest pain score.

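### The blinding statement makes no exception for the block performer, who must know the allocation, and perioperative opioid use counts fentanyl given to place the block, which cannot reflect block duration

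*Protocol*

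**What the plan says.** **Blinding.** The protocol's Blinding section states that investigators, research staff and patients will not know which treatment was given, and adds: "All providers, who administer pain medications to the patient, will be blinded to their treatment assignment". It names no exception.

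**Allocation.** Under Method of Assigning Subjects to Treatment Groups, the assignment is held in a "sealed, opaque envelope that will be provided only to the anesthesia provider performing the block".

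**Opioid at block placement.** Administration Instructions opens its list with "For the placement of the interscalene block, the patient may receive any of the following medications" and includes "Fentanyl: 0-100mcg IV". The text on the interscalene block under Other Clinical Procedures adds: "Light sedation is usually administered via the patient's IV during performance of the block". Neither place says who gives these drugs.

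**Endpoint.** Secondary Efficacy Endpoints defines perioperative opioid use so that "total opioids used preoperative, intraoperative, and postoperatively will be recorded". The synopsis, under Secondary Objectives, gives the reason for expecting a difference: a longer-lasting intraplexus block should lower opioid consumption.

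**Follow-up.** Other Clinical Procedures says: "On postoperative day 1, an anesthesiologist will call the patient". It requires the onset assessor to have had no part in placing the block, but sets no such condition for the caller.

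**The concern.** Two problems meet here.

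First, the design cannot have the blinding that the protocol claims. The arms differ only in where the needle goes, so the person holding it knows the arm. Because the protocol does not say so, it also does not say what that person may and may not do afterwards.

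Second, the opioid endpoint adds together two different things: fentanyl given so that the patient tolerates the procedure, and opioid needed once the block should be working. Only the second can show the effect in the hypothesis. If the two techniques differ in discomfort, or if an unblinded provider sedates the arms differently, that difference appears in the endpoint as though the block had saved or cost opioid.

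At stake are the interpretation of perioperative opioid use and, through the day-1 call, the credibility of the patient-reported secondary outcomes (block duration, pain, satisfaction).

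**Working it through.** The protocol gives no figure for this point that could be reproduced. The check compares the sections, followed by a short piece of arithmetic.

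**1. Who knows the allocation.** The envelope goes to the block performer. The technique is one injection between C5 and C6, or injection around the plexus, so the performer must know the arm. The Blinding section exempts nobody. Read literally, the two sections cannot both hold if the performer is an investigator, a member of the research staff or a giver of pain medication.

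**2. Who gives opioid, and whether it counts.**

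| Stage | Opioid in the protocol | Giver named? | In the endpoint? |
| --- | --- | --- | --- |
| Block placement | fentanyl 0-100 mcg | no | yes (preoperative) |
| Induction | fentanyl 0-50 mcg | no | yes |
| Intraoperative | fentanyl as needed, no stated ceiling | an anesthesia provider; not said whether this is the block performer | yes |
| Recovery room | fentanyl 0-350 mcg, among others | no | yes |
| To postoperative day 1 | consumption recorded at Visit 2 (Appendix 1) | not applicable | yes |

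The Blinding section would require a blinded giver at each stage where staff give the drug. No role rule puts this into effect.

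**3. Why the first row differs from the rest.** It is given to place the block, before the block can act. The protocol itself gives reasons why the arms might differ. Overview of Clinical Studies contrasts a single injection with multiple circumferential injections, and Risk / Benefit Assessment expects possibly more transient paresthesia with the intraplexus approach. These could push in opposite directions, so the sign cannot be predicted.

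**4. Effect on the comparison.** Write each patient's total as T = B + L, where B is block-placement opioid and L is all later opioid. Then:

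difference in mean T = difference in mean B + difference in mean L

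Only the last term can carry an effect of block duration. Any difference in mean B is added in full. Since B lies between 0 and 100 mcg of fentanyl, that difference cannot exceed 100 mcg in either direction. This is a limit, not an estimate.

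**5. Noise, as distinct from a shift.** Assume, for illustration only, that B is uniform on 0-100 mcg and recovery-room fentanyl is uniform on 0-350 mcg, independently.

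- SD of B = 100/√12 = 28.9 mcg
- SD of recovery-room fentanyl = 350/√12 = 101.0 mcg
- SD of the sum = √(28.9² + 101.0²) = 105.1 mcg
- Ratio = 105.1/101.0 = 1.04

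Under these assumptions the SD rises by about 4%, and by less if the other stages add independent variation. Lost precision is minor. The issue is a possible systematic shift.

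**The case against.** **The documents do not say that the block performer gives the fentanyl.** This stands. A reader might infer a flat contradiction on fentanyl, but the wording at both places is passive, and the performer is named only as preparing and dispensing the ropivacaine. A blinded colleague could give the sedation. The protocol leaves the breach open; it does not prescribe it.

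**The Blinding section already bars an unblinded giver of later analgesia.** This also stands. A reader might infer that the block performer is free to give intraoperative fentanyl, but the general sentence on blinded providers rules that out. What is missing is a rule on roles that makes the sentence workable. The statement about investigators and research staff arguably covers the day-1 caller too. Yet that same statement is silent on the performer, and the protocol writes an explicit separation only for the onset assessor.

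**The endpoint window is an openly stated choice, and an SAP could split it by period.** This stands in part. A total is a legitimate quantity, and extra fentanyl needed for a less comfortable technique is a real consequence of allocation. It is still not a consequence of block duration, which is the reason the protocol gives for expecting a saving. An SAP could refine the window, but it cannot make the blinding statement true.

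**The amounts may be small.** A reader might compare 100 mcg with the recovery-room ceiling and read 100/450 = 22% as the share of the endpoint at risk. The documents do not support that. It is a ratio of two ceilings, and it omits induction fentanyl, intraoperative fentanyl without a stated limit, and opioid use after discharge. The protocol also says that sedation is minimized so that patients can report paresthesias.

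**Conclusion.** The point holds in two parts. The blinding statement cannot be true as written, because the block performer must know the allocation and no exception is made. Separately, and whoever gives it, block-placement fentanyl is counted in an endpoint whose hypothesis rests on block duration, which that fentanyl cannot reflect.

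The size of any resulting arm difference is unknown. The documents give only the per-patient range of 0-100 mcg, and no figure for typical use or for a difference between techniques. That the techniques may differ in the need for sedation is an inference from the protocol's description of them.

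Only secondary endpoints are affected. A reader might extend the concern to the primary endpoint, but time to loss of shoulder abduction is assessed by an investigator who took no part in placing the block. The point is worth correcting because the correction is cheap, not because the trial's main conclusion is in danger.

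**What to change.** 1. **Opioid endpoint.** Use opioid consumption from operating-room entry through the day-1 call as the endpoint that tests the block's effect. Report block-placement opioid separately by arm. The total can still be shown.
2. **Blinding wording.** Name the block performer as unblinded, and describe the trial as patient- and assessor-blinded.
3. **Roles.** Reconcile Blinding, Method of Assigning Subjects to Treatment Groups, Administration Instructions (block placement and intraoperative analgesia) and Other Clinical Procedures, so that it is clear who gives and records opioid at each stage.
4. **Day-1 call.** Extend to the caller the separation from block placement that already applies to the onset assessor.
5. **Repeat block.** State how the postoperative evaluation for a repeat block fits the Blinding section. This asks only that the sections be reconciled; no dose or clinical rule needs to change.

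The cost is wording, role assignment and one more reported quantity. The Blinding section already promises blinded analgesia providers, so extra staff should not be needed, although that is an inference.
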